### Informed consent

2.5

From the informed consent discussion and form, the intervention, risks, benefits, and patient's rights in the study will be explained in a simple language that patients can clearly understand (by an hospital doctor). The informed consent will be signed by the patient or by a legal guardian. In the circumstance that they wish to withdraw from the study, our strategy is to use the available data for the final analyses and accommodate the patients’ wishes accordingly.

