### Outcome measures

2.13

The main outcome measurement will be the pain levels of both rest and mobile status for the BCT patients (the mobile status includes cough, deep breath, and turn over on the bed). The patient will measure their pain according to 3 subjective pain scales, namely the NRS, and FRS before treatment, 30 minutes after treatment and 4 days after the press tack needles/placebo intervention. Furthermore, a follow-up will assess the NRS pain scale telephonically at 14 days and 3 months after the initial intervention.

Secondary outcome measurements will include the improvement of respiratory function, sleep quality, and amount of medication used (specifically analgesics and muscle relaxants). We used the portable triflow flowmeter and VSH sleep scale as objective tools for the aforementioned purposes. The patients will be educated on the use of the flowmeter by the affiliated thoracic surgeon. Patients will be allowed as much time as needed to practice the use of the flowmeter before the first measurement is taken. When the patient is ready, the study personnel will commence the measurements of 3 attempts, and will record the best 2 attempts. The triflow flowmeter measures the amount of air the patient can exhale; it has 3 chambers with their own balls that require air pressures from 600 to 1200 cm^3^ per second to elevate. 1200 cm^3^ is the highest score and indicates good exhalation power. The above process will be done before intervention, 30 minutes after intervention and 4 days after the intervention. The patient will also answer the VSH sleep scale in Mandarin to evaluate the sleep quality of the night before the clinic visit. They will complete the questionnaires accordingly at every clinic visit, for a total of 2 times (on day 1 and day 4). Finally, on the 4th day after the initial intervention, participants will bring back the prescribed medication, including analgesics and/or muscle relaxants that were left unused, to be measured for the amount of medication used.

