### Sample size calculation

2.16

In a previous similar study,^[11]^ the pain scale reduced significantly as recorded immediately after acupuncture treatment. We utilized the result of this study to calculate sample size as generated by G∗power version 3.1.9.2 software. Accordingly, in the condition of 95% power being calculated with an effect size of 1.124365. The patient number in each group should be a minimum of 18 participants. However, we also considered that a previous study included 29 patients in each group with a total of 58 patients. With respect to a dropout rate of 20%, we decided to include 36 patients in each group, for a total of 72 patients.

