### Statistical analysis

2.19

Statistical analyses will be performed using SPSS software version 22.0 (SPSS Inc, Chicago, IL). The demographic data between Acu and Con groups including gender, age, and clinical characteristics will be compared using the Student's *t* test and Chi-squared test. Between-group values will be measured by the paired *t* test. For the multiple pain scale and sleeping quality measurements, a one-way ANOVA will be used according to the previous similar study.^[11]^ We will also implement the advanced repeat measurement analysis in the study. Data will be presented as mean ± standard deviation. A *P*-value of less than .05 will be considered statistically significant.

Subgroup analysis will be done based on the following: age, sex, number of treatments complete, number of hours of needle retention, number of rib fractures, pulmonary complications, hospitalization, number of days from patient's injury to the first treatment, Triflow score, medication use, body mass index, and ISS. In cases of small sample size, the Mann–Whitney *U* and the Wilcoxon sign rank test will be implemented accordingly. Missing data will be analyzed using the pairwise deletion method.

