
### Limitations

3.1

The study provides an effective intervention but is limited to a shallow acupuncture needling depth of the superficial subcutaneous layers and cannot be associated with the benefits caused by the deeper stimulations commonly associated with most acupuncture interventions. Furthermore, the point selection in this study only concentrates on anterior and lateral BCT locations. Lastly, the follow-up method of telephone calls at 14 days and after 3 months can prove problematic, and a high loss to follow-up is anticipated.

In this study, we offer a simple, low-cost form of acupuncture that, if it will prove superior analgesic effects in comparison to the placebo, can provide a safe and reasonable treatment alternative to BCT patients.

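### Pairwise deletion leaves the 14-day and 3-month pain contrasts open to bias from selective non-response, where the protocol itself expects high loss

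*Protocol article*

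**What the plan says.** The Statistical analysis section (2.19) gives one rule for incomplete data: "Missing data will be analyzed using the pairwise deletion method". It assigns the repeated pain scores to a one-way ANOVA and then adds: "We will also implement the advanced repeat measurement analysis in the study". It does not name that model or say how it relates to the deletion rule.

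Under Outcome measures (2.13), pain is scored on the NRS and "FRS before treatment, 30 minutes after treatment and 4 days after the press tack needles/placebo intervention". The later scores come by telephone: "a follow-up will assess the NRS pain scale telephonically at 14 days and 3 months after the initial intervention". These calls are described in the paragraph on the main outcome.

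The Limitations section (3.1) says that the telephone calls "can prove problematic, and a high loss to follow-up is anticipated". It gives no rate. The only rate is in the Sample size calculation (2.16): "With respect to a dropout rate of 20%, we decided to include 36 patients in each group, for a total of 72 patients". For patients who withdraw, the Informed consent section (2.5) says "our strategy is to use the available data for the final analyses".

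**The concern.** For a between-arm difference at one visit, pairwise deletion means comparing whoever has a value at that visit. A patient's day-4 score still counts in the day-4 contrast. It is not used at 14 days or 3 months to allow for the fact that this patient is missing.

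That matters if day-4 pain predicts both later pain and whether the patient answers the telephone. Recovered patients may have little reason to answer, and the Discussion cites pain falling to 2 to 3 points after 15 days. If acupuncture lowers day-4 pain, one common rule, that low-pain patients answer less often, removes more patients from the acupuncture arm and selects them more strongly. The observed difference then shrinks although nobody behaves differently because of allocation. At stake are the two later pain contrasts, at the visits where the protocol expects loss.

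**Working it through.** **The protocol's own figure.** The 20% dropout allowance reproduces: 29 / 0.80 = 36.25, set at 36 per arm; conversely 36 x 0.80 = 28.8. The protocol gives no separate rate for the telephone calls, so every loss rate below is an assumption.

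**Illustration 1: size of the bias at 14 days.** Assumed, not in the protocol: SD 2 at each visit, correlation 0.6 between day 4 and day 14, true difference (acupuncture minus placebo) -1.0 at both visits, and non-response that is logistic in day-4 pain, with low-pain patients answering less often.

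With equal SDs, each arm's day-14 mean among responders moves by 0.6 times the shift in that arm's day-4 mean. So:

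observed difference = true difference + (shift in acupuncture mean) - (shift in placebo mean)

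- Slope -0.5 per point, loss 33% placebo and 43% acupuncture: the day-14 means shift by 0.34 and 0.43, and -1.0 + 0.43 - 0.34 = -0.91. Simulations with 1,000,000 patients per arm gave -0.90 to -0.91.
- Slope -0.8 per point, loss 33% and 46%: the shifts are 0.45 and 0.61, and -1.0 + 0.61 - 0.45 = -0.84. Simulations gave -0.83 to -0.84.
- Regression on the day-4 score returned about -1.0 in both cases.

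**Bias against sampling error.** With 36 randomised per arm, 33% and 43% loss leave 36 x 0.67 = 24.1 and 36 x 0.57 = 20.5 patients. The standard error is 2 x sqrt(1/24.1 + 1/20.5) = 0.60, so a bias of 0.10 is 0.10 / 0.60 = 0.17 of a standard error. With 46% loss in acupuncture, 36 x 0.54 = 19.4 remain, the standard error is 0.61, and a bias of 0.16 is 0.16 / 0.61 = 0.26 of it.

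**Illustration 2: dependence on the mechanism.** Five visits, SD 2, common correlation 0.6, true 3-month difference -1.0, about 40% missing at 3 months, 20,000 patients per arm. The likelihood estimate uses all visits with unstructured means and covariance in each arm.

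| Loss depends on | Available cases | Likelihood estimate |
|---|---|---|
| Nothing (random) | -1.01 | -1.01 |
| Baseline pain, same rule in both arms | -0.99 | -0.99 |
| Day-4 pain, same rule (high-pain patients lost) | -0.86 | -1.03 |
| Day-4 pain, opposite direction by arm | +0.12 | -1.00 |
| Unseen 3-month pain, same rule | -0.71 | -0.82 |
| Unseen 3-month pain, opposite direction by arm | +0.85 | +0.05 |

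The first two rows show no bias from available cases. The middle two show bias that the earlier scores remove. The last two show bias that no use of observed scores fully removes.

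**Precision at 36 per arm.** The SD of the estimate, available cases against likelihood, was 0.65 against 0.60 under random loss, 0.60 against 0.65 under the common day-4 rule, and 0.58 against 0.68 under the opposed day-4 rule. Neither method is uniformly more precise.

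**The case against.** The strongest reply is that the bias is hypothetical and small. The protocol states neither the loss rate nor the mechanism, and its only rate is 20%. Under the common-rule illustration the bias at 14 days is 0.10 to 0.17 points, towards no difference and well inside one standard error. The planned repeated-measures analysis might already be a mixed model, with details in a fuller document, and available data are to be used after withdrawal. The sample size is built on the immediate effect, and no high loss is expected at 30 minutes or day 4. All of this stands, and it limits the reach and weight of the point. It does not remove the point, because pairwise deletion is a method the text states, not a detail left open.

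A reader might infer more than the protocol supports:

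- **That the later contrasts are certainly biased, or unbiased only if loss is unrelated to arm or earlier pain.** Loss that differs by arm but is otherwise random leaves each arm's mean unbiased, and loss on baseline pain by the same rule gave -0.99.
- **That a mixed model cures the problem at no cost.** It is valid under missing at random. With opposed loss on unseen pain it gave +0.05 against a true -1.0. It also adds assumptions about means, covariance and normality, the last doubtful for scores near the bottom of the scale.
- **That patients with any missed visit would be dropped altogether.** This follows only if the unnamed repeated-measures analysis is a classical ANOVA, which the protocol does not say.

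**Conclusion.** The point holds as a risk confined to the 14-day and 3-month NRS contrasts. The protocol expects substantial loss there, fixes a rule that makes no use of earlier scores for those contrasts, and does not reconcile that rule with the repeated-measures analysis it also names. Under one common non-response rule based on day-4 pain, the bias in a 1-point difference is about 0.1 to 0.17 points; it is larger only under more extreme mechanisms. These sizes rest on an assumed SD of 2, a correlation of 0.6, loss of 33% to 46% and a logistic mechanism, none of them in the protocol. The argument rests on bias, not on precision. The change is worth making before the data are analysed, but the point does not undermine the trial's early pain results.

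**What to change.** In section 2.19, limit the deletion rule and name the model for the NRS. Suggested wording:

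> NRS pain scores will be analysed by a likelihood-based linear mixed model (SPSS MIXED) with arm, visit and arm-by-visit terms and a pre-specified covariance structure. It will use all available scores of all randomised patients in their allocated group, including scores recorded before withdrawal. For the 14-day and 3-month contrasts this model replaces pairwise deletion and the one-way ANOVA. It assumes that scores are missing at random. In a sensitivity analysis at 14 days and 3 months, missing acupuncture-arm scores are shifted upward by increasing amounts (delta) until the conclusion changes.

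The delta analysis is needed because the model does not deal with loss driven by unobserved pain. It is easy to read: a delta of 1 point with 43% missing in the acupuncture arm moves that arm's mean by 1 x 0.43 = 0.43 points. The rule for the other outcomes, such as medication counts, should be kept or restated separately so that they are not left without one.

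The cost is modest extra analysis work and the added model assumptions, including normality for scores near the scale floor. A gain in precision at 36 per arm is not guaranteed. No sample-size figure, visit or assessment changes.

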## Discussion

3

The nociceptive response is a reflexive bodily response of the body aimed at providing protective mechanisms. In short, pain creates awareness of pathological conditions resultant from injury or harm, and may vary in intensity, quality, duration, and referral. Accordingly, pain is categorized according to 4 distinct types: nociceptive pain, inflammatory pain, neuropathic pain, and functional pain.^[12]^ In the case of BCT, nociceptive signals are transmitted to the brain following peripheral tissue damage. In terms of the 1 to 10 NRS pain scale, the patient's pain levels on the first recorded day of injury can reach up to 9 to 10 points, whereafter the pain sensation gradually decreases and is subsequently recorded at reduced levels of 2 to 3 points after 15 days.^[13]^ However, the long term effects of pain resultant from physical injury usually display concurrent overlapping conditions related to the physical, psychological, and even socio-economic function ability of patients, and can last up 12 months after initial injury.^[14]^

Acupuncture treatment is well known for its analgesic potential, with proven efficacy particularly in chronic pain conditions. Furthermore, the therapeutic benefits of this treatment are extended to complicated conditions of maladaptive pain, such as myofascial pain, tension headache, irritable bowel syndrome, etc.^[15–19]^ In terms of acute pain, acupuncture has displayed promising analgesic effects in a wide array of diseases, with particular emphasis on emergency medicine.^[20–22]^ Furthermore, acupuncture has displayed tendencies of increased efficacy in the treatment of bone fractures as shown in elders in the acute stage of hip fracture. In addition, patients who received acupuncture treatment in the ambulance en route to hospital, reported reduced pain sensations, less anxiety, and lower heart rates. They also stated a higher overall satisfaction regarding the emergency ride to the hospital.^[22]^

The analgesic effects of acupuncture have been further biochemically described via research obtained from various animal studies. The underlying molecular mechanisms of acupuncture analgesia are commonly associated with an increase in adenosine and an upregulation of the A1 receptors that are largely associated with anti-nociceptive effects.^[23]^ Other possible explanations of acupuncture analgesia include the evident reduction in common inflammatory mediators such as substance P, IL-1β, IL-8, IL-10, and TNF-α, all of which are over-expressed in nociceptive hypersensitive states, specifically inflammatory pain, and functional pain conditions.^[24]^

Current literature contains limited information with regards to the use of acupuncture treatment in cases of BCT. Accordingly, only 1 randomized control trial and 1 case report about the benefit of acupuncture for the blunt chest injury was discovered.^[11,25]^ In the randomized control trial, Ho et al focused on the patients with 2 or more rib fractures requiring hospital admission (level 3). These patients were usually well monitored and treated with adequate analgesic mediations during their hospital stay. When patients classified according to level 1 or level 2, without rib fractures or with less than 2 fractures, respectively, are treated in the out-patient clinic, the pain control measures are limited, especially when intravenous (IV) medications are not available.

To this end, acupuncture provides suitable, reliable, and effective forms of relief for these patients. The efficacy of Chinese Medicine in the treatment of various conditions has been proven over thousands of years.^[26]^ Doctors discovered that the injuries of internal organs or the torso could be treated via the stimulation of the distal skin surface, such as the limbs, ears, or skull. They drew lines to connect specific points, and developed a map of the 14 meridians, each of them is related to a specific organ system.^[27]^ In the present study, we utilize this concept through the use of distal point stimulation of 4 limbs to ease the chest pain associated with traumatic incidences without directly applying needles at the site of injury.

With regards to the manipulation of acupuncture needles for increased therapeutic benefit, a multitude of options are available, including manual acupuncture, electro-acupuncture, press tack needle, laser acupuncture, etc.^[28]^ For this protocol, we had chosen the press tack needles and press tack placebo due to their simplicity and similarity which allows for effective blinding. The press tack needles look identical to the press tack placebo, whereby one can only see a difference at the time of needle insertion and withdrawal upon extremely close inspection of the needles, and thus they can serve as an ideal device to generate the “blindness” effect to both the patients and the acupuncturist.^[10]^ The “De Qi” phenomena, which is usually achieved through manipulation of the acupuncture needles via rotation is considered by some as a major part of the acupuncture effect, and might be lost in the application of press tack needles, thus being regarded as the press tack needles’ biggest disadvantage.^[29,30]^ However, as we want to apply the use of acupuncture in a conventional allopathic, we believe that the press tack needles can provide a simple to use and safe treatment option for all modalities of medical care. In this study protocol, we decided to implement the following acupoints: GB 34 (YangLingQuan), GB 36 (Waiqiu), LI 4 (HeGu), LU 7 (LieQue), ST 36 (Zusanli), TH 5 (Waiguan), as a result of similar theoretical affiliations. Specifically, the concept associated with these specific points is directed at the fact that most chest trauma occurs on the frontal and lateral areas of the chest. Accordingly, Chinese medicine theory describes the frontal area of the chest as being controlled by the yang ming layer (stomach and large intestine meridians), to which end the acupoints: LI 4 (HeGu) and ST 36 (Zusanli) belong to that layer and can potentially generate an analgesic effect within the specified area. The lateral side of the chest is purportedly controlled by the shao yang layer (gall bladder and triple warmer meridians), whereby the acupoints GB 34 (YangLingQuan), GB 36 (Waiqiu), and TH 5 (Waiguan) can potentially improve Qi and blood flow within this specific region and alleviate pain.^[29,31]^ The addition of the acupoint LU 7 (LieQue) was designed to treat the lung organ and improve lung functions.^[32]^ The acupoints ST 36 (Zusanli) and LI 4 (HeGu) were found to decrease incisional pain and improve post-operative rest in post abdominal surgery patients.^[33]^ The acupoints LU 7 (LieQue), LI 4 (HeGu), ST 36 (Zusanli), TH 5 (Waiguan) also showed a general analgesic benefit and increased post-operative recovery.^[34]^

### Limitations

3.1

The study provides an effective intervention but is limited to a shallow acupuncture needling depth of the superficial subcutaneous layers and cannot be associated with the benefits caused by the deeper stimulations commonly associated with most acupuncture interventions. Furthermore, the point selection in this study only concentrates on anterior and lateral BCT locations. Lastly, the follow-up method of telephone calls at 14 days and after 3 months can prove problematic, and a high loss to follow-up is anticipated.

In this study, we offer a simple, low-cost form of acupuncture that, if it will prove superior analgesic effects in comparison to the placebo, can provide a safe and reasonable treatment alternative to BCT patients.
